For families in which both caregiver and youth give informed consent and assent and complete screening, the tablet automatically (1) randomizes the family to study condition, using urn randomization to achieve balanced allocation of participants based on sex, race, ethnicity, and age group; and (2) computes a risk category. In SBIRT-A-Standard, the risk category (*low risk*, *riding risk only*, *distant use*, or *recent use*) is assigned using youth screening data only, while SBIRT-A-Family uses youth plus caregiver screening data to assign the risk category (*low risk*, *hidden substance use risk*, *named mental health risk*, or *named substance use risk*). For youth and families assigned to the *low risk* category (ie, no positive screen result), youth are invited to view tablet-delivered psychoeducation slides, and caregivers are invited to view a video tour and enrollment link to web-based educational and support resources for adolescent AOD. For youth and families assigned to an *at risk* category, youth and caregivers each view tablet-delivered psychoeducation videos and (for some risk categories) complete provider-facing BI and RT activities that are differentiated based on condition assignment and tailored to the respective risk categories. Multimedia Appendix 2 summarizes study activities for each condition; full descriptions are provided in the Study Conditions subsection. All study providers are trained to deliver both SBIRT-A approaches (ie, provider crossover design).

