Every adolescent or family assigned to an *at risk* category in either condition is enrolled until study capacity is reached (n=2000). In addition, a randomly selected subsample of adolescents (n=300; balanced across conditions) screened as *low risk* are followed for outcome assessments; the selection of the group categorized as *low risk* uses quota sampling based on sex, race, ethnicity, and age. Outcome data are collected via remote digital assessment methods at initial assessment (as soon as possible after the PC visit) and at 3, 6, 9, and 12 months after the PC visit using REDCap Cloud software (Research Electronic Data Capture developed at Vanderbilt University and licensed to cloud-based technology company nPhase, Inc), a widely used secure, Health Insurance Portability and Accountability Act (HIPAA)–compliant, web-based data collection platform. Figure 2 shows the SPIRIT (Standard Protocol Items: Recommendations for Interventional Trials) checklist depicting the schedule of trial enrollment, interventions, and assessments. All youth and caregivers separately receive both email and SMS text prompts when assessments are due, using contact information provided during the consenting process. When either youth or caregiver fails to complete a follow-up assessment, research staff members blinded to condition assignment reach out to arrange a live assessment via telephone or videoconference. Each assessment requires approximately 20 minutes to complete.

Clinicians and families enrolled in the study retain the right to withdraw consent at any time. The protocol will be discontinued at any site where procedures become burdensome or otherwise impinge on the routine performance of participating staff. Analysis of intervention impacts and potential harm will be continuous throughout the trial. In cooperation with the administration of the partnering sites, investigators will provide full study debriefing and offer counseling referrals to any participant aggrieved or injured due to trial participation.

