### SBIRT-A-Standard Procedures

#### Screening (Approximately 2 Min)

All consented youth aged 12 to 17 years complete the CRAFFT (car, relax, alone, forget, friends, trouble) screening tool [54,55], which assesses the number of days during the past year and then the past 3 months during which various formulations of AOD were used, as well as whether they have ridden in a car whose driver was intoxicated; youth who respond negatively to all questions are categorized as *low risk*. If youth report >0 days of AOD use, the tool asks 5 additional questions assessing use risk and consequences; in addition, youth who report nicotine use in the past 30 days complete a nicotine dependence measure, the Hooked on Nicotine Checklist [56], modified to include nicotine vaping. Screening data are then used to sort youth into 3 risk categories: *riding risk only* (no reported AOD use but indicated rode in car driven by intoxicated person), *distant use* (reported AOD use in past year but not past 3 months), or *recent use* (reported AOD use in past 3 months). All screening data are summarized in a tablet-delivered clinician report to guide provider-facing intervention activities.

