### SBIRT-A-Family Procedures

#### Screening (Approximately 2 Min Apiece)

Screening procedures incorporate CRAFFT procedures for youth described for the SBIRT-A-Standard condition. They also incorporate two sources of caregiver-report data: (1) an assessment of caregiver beliefs about their child’s AOD use and worries about the impact of AOD use, and (2) a well-validated checklist of youth mental health problems [67] that yields clinical cut scores for 4 domains. If both youth and caregiver report no AOD use or clinically elevated mental health problem, the family is categorized as *low risk*. Otherwise, screening data are combined to sort families into 3 risk categories: *hidden substance use risk* (youth reports AOD use in past year; caregiver reports no youth AOD use in past year), *named mental health risk* (caregiver reports no youth AOD use in past year; caregiver reports clinical-level score for at least 1 youth mental health domain), and *named substance use risk* (caregiver reports youth AOD use in past year with or without reporting a clinically elevated mental health score). Adolescent and caregiver screening data are both summarized in the clinician report to guide provider-facing intervention activities.

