**(1)**

**(2)**

wherein (1) and (2) are jointly estimated submodels for the SBIRT-A-Standard and SBIRT-A-Family conditions, respectively. The dependent variable in each equation is the log odds (*logit*) that AOD use response *Y* for person *i* at time point *j* (*j*=1 to 5) is in category *c* (*c*=1 to *C*−1) or lower where *c* is one of the ordinal response categories created from the AOD measure. The *b*_0_*_i_* parameters in (1) and (2) are random intercepts estimating the log odds of *Y_ij_*≤*c* at initial assessment in each condition; the *b*_1_ parameters estimate the linear rate of change (ie, slope) in the log odds of *Y_ij_*≤*c* across measurement points, which are indexed by the variable *TIME_j_*. The *γ_c_* parameter estimates thresholds between adjacent categories on the given AOD variable. The intercept in each submodel is specified as a random effect to account for the nesting of repeated measurements within individuals. Slope parameters are specified as fixed effects. The model is specified as jointly estimated simultaneous equations for each study condition, rather than a single model containing an intervention main effect and interaction term, to allow for greater flexibility in modeling group-specific effects as well as for comparing each condition to the normative comparison (NC) group of youth (in which the given youth, standard condition or youth and family, family condition, screened negative). Changes in the levels of AOD use are captured by the *b*_1_ parameters in each submodel, where positive values of *b*_1_ indicate an increase in the log odds of being in a lower AOD use category on each logit over time compared to the initial assessment. The causal effect of assignment to SBIRT-A-Standard versus SBIRT-A-Family on AOD use (ie, the intent-to-treat effect) is estimated as the difference between *b*_1_*_,sbi−fam_* and *b*_1_*_,sbi_*_._ Separate models are fitted for each AOD use outcome variable. To account for nonindependence due to the clustering of individuals within clinic sites, indicator variables controlling for the fixed effect of each clinic will be included as covariates in submodels (1) and (2) [95].

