#### Evaluating Clinical Significance

The clinical significance of intervention effects on youth AOD use at 1-year follow-up is evaluated by gauging the degree to which youth identified as at risk resemble youth in the NC group, which provides a normative benchmark against which to compare changes in AOD use in the 2 study conditions. Analyses are performed by adding a third submodel to those shown in (1) and (2) that estimates change in AOD use levels between initial assessment and 1-year follow-up among NC youth. By definition, 100% of NC youth are in the *none* AOD use category at initial assessment. On the basis of preliminary analyses using data from the NSDUH, this percentage is expected to decline to approximately 90% at 1-year follow-up, whereas increases are expected in both study conditions. The difference in the likelihood (ie, log odds) of reporting AOD use in the *none* category at 1-year follow-up in each study condition compared to the NC group is quantified in the following equations:

NC versus SBIRT-A-Standard: [(*b*_0_*_i_*_,_*_no−risk_* + *b*_1,_*_no−risk_* × 4 + *γ*_1_) – (*b*_0_*_i_*_,_*_sbi_* + *b*_1,_*_sbi_* × 4 + *γ*_1_)] **(3)**

NC versus SBIRT-A-Family: [(*b*_0_*_i_*_,_*_no−risk_* + *b*_1,_*_no−risk_* × 4 + *γ*_1_) – (*b*_0_*_i_*_,_*_sbi−fam_* + *b*_1,_*_sbi−fam_* × 4 + *γ*_1_)] **(4)**

where *b*_0_*_i_*_,_*_no−risk_* and *b*_1,_*_no−risk_* are the intercept and slope parameters in the mixed effects longitudinal logistic regression submodel for the group, *4* is the coded value for *TIME_j_* at 1-year follow-up, and *γ*_1_ is the threshold for the *none* category on AOD use variable *Y*. A log odds value of 0 resulting from the aforementioned differences indicates equivalence between the groups, whereas positive log odds values indicate a higher likelihood of reporting *none* at 1-year follow-up in the NC group. These differences are converted into odds ratios and then into Cohen *d* values using an “odds ratio to *d*” conversion formula [96]. The Cohen *d* value between the NC and SBIRT-A-Family groups is expected to be in the *small* range (0.10-0.30), and the Cohen *d* value for the NC versus SBIRT-A-Standard comparison is expected to be in the *moderate* range (0.40-0.60). Small effect size values would indicate high concordance in AOD use between the NC group and the at-risk study categories, thereby supporting the clinical significance of intervention effects at 1-year follow-up.

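### The normative comparison group pools low-risk youth chosen by two different rules, one per arm, which probably lowers the norm used to judge clinical significance

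*Protocol article*

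**What the plan says.** Under Recruitment, Randomization, Intervention Flow, and Outcome Assessment Procedures, the Standard risk category "is assigned using youth screening data only, while SBIRT-A-Family uses youth plus caregiver screening data to assign the risk category". The same section follows "a randomly selected subsample of adolescents (n=300; balanced across conditions) screened as" low risk, so about 150 come from each arm.

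The two screening sections set the rules:

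- **Standard:** "youth who respond negatively to all questions are categorized as" low risk. Caregiver data play no part.
- **Family:** "If both youth and caregiver report no AOD use or clinically elevated mental health problem, the family is categorized as" low risk.

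Aim 1 Analyses states the double definition openly. The normative comparison (NC) group is the one "in which the given youth, standard condition or youth and family, family condition, screened negative".

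Evaluating Clinical Significance then treats the group as one population. It "provides a normative benchmark against which to compare changes in AOD use in the 2 study conditions", and the analysis is done by "adding a third submodel to those shown in (1) and (2) that estimates change in AOD use levels" among NC youth. One NC intercept and one NC slope enter both equation (3) (NC versus Standard) and equation (4) (NC versus Family). No term for arm or definition within the NC group is described. All NC youth start in the *none* category, and "this percentage is expected to decline to approximately 90% at 1-year follow-up".

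**The concern.** Take a youth who answers every question negatively but whose caregiver reports AOD use, or a clinical-level score in a mental health domain. In Family this youth falls into a named risk category and belongs to the arm being judged. In Standard the same youth is eligible for the norm. Equation (4) can therefore have the same kind of youth on both sides.

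The protocol argues that these youth are not typical low-risk youth. Its introduction says that caregiver report is particularly useful when youth minimize their use, and that co-occurring behavior problems both signal and worsen AOD risk. If so, their presence in half of the norm pulls down the NC *none* rate at 1 year. The plan reads a small distance from the norm as support for clinical significance, so the error would favor that conclusion for both arms.

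**Working it through.** **Inputs from the protocol.** NC *none* rate at 1 year: about 90% (AOD use, Evaluating Clinical Significance). At-risk rates at 1 year: 78.4% Family and 67.9% Standard (alcohol, Study Power). Expected d: 0.10-0.30 for NC versus Family and 0.40-0.60 for NC versus Standard. NC sample: 300, half from each arm.

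**Formula.** The plan converts log odds differences to Cohen d but does not print the formula. I assume the usual one: d = [logit(p_NC) − logit(p_arm)] × √3/π. I apply it to marginal proportions. The plan's random-intercept model works with subject-specific log odds, so its values will differ in scale.

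**The plan's own figures.** With 0.90 against 0.784 and 0.679, d = 0.50 and 0.80. The expected bands are not reproduced. They would need an NC rate of about 81-86%. The 90% is for any AOD use and the arm rates are for alcohol, so this is not a strict check, and it is a separate matter. It does mean that the bands serve only as a scale here.

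**Effect of pooling.** Let f be the share of youth-negative families that the caregiver flags. The protocol gives neither f nor *none* rates by flag. I assume f = 10-30%, with 12-month *none* of 92% in unflagged and 80% in flagged youth, and take the Family half to be all unflagged.

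- Standard half: p_S = (1 − f) × 0.92 + f × 0.80
- Pooled norm: p = 0.5 × p_S + 0.5 × 0.92
- Shift in d: [logit(0.92) − logit(p)] × √3/π, with logit(0.92) = 2.442

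| f | Flagged among 150 | Standard half | Pooled norm | Shift in log odds | Shift in d | d, NC v Family | d, NC v Standard |
|---|---|---|---|---|---|---|---|
| 0 | 0 | 92.0% | 92.0% | 0 | 0 | 0.64 | 0.93 |
| 0.10 | 15 | 90.8% | 91.4% | 0.079 | 0.04 | 0.59 | 0.89 |
| 0.20 | 30 | 89.6% | 90.8% | 0.153 | 0.08 | 0.55 | 0.85 |
| 0.30 | 45 | 88.4% | 90.2% | 0.223 | 0.12 | 0.51 | 0.81 |

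The gap between the last two columns is 0.30 in every row: the norm is common to both equations and cancels.

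**Other assumed rates.** Hold the pooled norm at the stated 90% and vary the halves. With 91% (Family) and 89% (Standard), the shift from the Family-only norm is 0.565 − 0.501 = 0.06. With 92% and 88% it is 0.636 − 0.501 = 0.14. With 95% and 85% it is 0.913 − 0.501 = 0.41. That last case needs flagged youth at (0.85 − 0.7 × 0.95)/0.3 = 62% even if 30% are flagged, which is below the 67.9% projected for at-risk Standard youth on alcohol. I do not rely on it.

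**Comparison with noise.** The sampling SE of the NC log odds at one time point, with n = 300 and p = 0.90, is √[1/(300 × 0.9 × 0.1)] = 0.192, or about 0.11 in d.

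**The case against.** The other side has good arguments, and several limit the point.

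- **The double definition is disclosed and the weighting is fixed.** A reader might infer that the norm drifts with the arm split or that its population is unknowable. Neither holds. The balance across conditions is set by design, and the group is what each arm's own procedure calls low risk. What remains is that the 50:50 mixture matches neither definition.
- **The reach is narrow.** A reader might infer that the pooled norm biases the comparison of Family with Standard. It does not. The aim 1 estimate is the slope difference between the two at-risk submodels and does not use the NC group, and the norm cancels between (3) and (4). Whether the at-risk groups are themselves alike is another question.
- **The gap between the halves is not the error.** On the assumed inputs the halves differ by d of 0.08-0.23, but the plan never compares them. The pooled shift, about half of that, is what counts.
- **The shift is modest against sampling error.** It is at most about one SE of the NC side. This stands as a matter of scale. It does not excuse the mixture, because the shift has an expected direction and more NC youth would not remove it.
- **The direction is not certain.** The outcome is youth self-report. Youth who deny use while a caregiver reports it may go on denying it. The protocol also says that caregivers typically underestimate use, which argues against a high flag rate for use. The concern about mental health flags is less affected.
- **Riding in a car with an intoxicated driver.** A reader might infer from the Family screening section, which does not name riding, that riding-only youth enter the Family half of the norm. The documents do not support this firmly. The recruitment section equates low risk with no positive screen result, and Family screening takes over the Standard youth procedure. The silence may be condensed wording, so it is a matter to reconcile and not part of the estimate. If such youth are included and carry added risk, the Family half falls as well and the gap between the halves narrows.

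**Conclusion.** The point holds in limited form. About 150 youth who are low risk on their own report and about 150 who are low risk on youth plus caregiver report are modelled as a single norm, although some of the former would count as at risk in the other arm. This probably lowers the norm and makes both arms look closer to it. The shift is about 0.04-0.12 in d if 10-30% are flagged and *none* is 92% in unflagged and 80% in flagged youth. The protocol supports neither assumption with a figure, and other assumed rates give other sizes. The upper end is more than half the width of the 0.10-0.30 band. Only the absolute reading of clinical significance is affected. It is worth correcting because correction is cheap, not because the trial's main comparison is at risk.

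**What to change.** Define the comparison group for the third submodel by one rule in both arms: no positive answer on the youth screen, no caregiver-reported AOD use, and no clinical-level Brief Problem Monitor domain. State how a caregiver's unsure answer about use is counted. Every family completes both screens before randomization, so the rule needs no new data and brings in no selection after randomization. Apply it to further comparison-group sampling. For youth already sampled, fit the submodel to those who meet the rule, and report the estimate from all 300 as a sensitivity analysis.

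The cost is that some Standard comparison youth (15-45 under the assumed flag rates) are replaced or set aside. If they are not replaced, there is a small loss of precision and some loss of balance across arms and demographic quotas. The norm will also be healthier than the Standard low-risk population, which the report should say.

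Separately, reconcile the recruitment section with the Family screening section on whether a youth whose only positive answer is riding can be low risk in Family.

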### Recruitment, Randomization, Intervention Flow, and Outcome Assessment Procedures

Study recruitment and randomization as well as all SBIRT-A activities occur on the day of the visit in PC offices. Figure 1 depicts the flow of patient recruitment, patient randomization, and SBIRT-A delivery for various risk categories. Recruitment efforts will be multimethod, consisting of (1) informational flyers in wait areas, (2) outreach to families by site research staff, and (3) warm handoff by site administrators and providers when needed. Interested caregivers are prompted to contact on-site research staff, who then give the designated caregiver a tablet to (1) complete an electronic research consent form, (2) provide family demographic and brief assessment information, and (3) complete a screening tool assessing their concerns about the adolescent’s AOD use and related behavior problems as well as family communication about AOD issues. Simultaneously, research staff give a tablet to the youth, who completes an electronic research assent form, and if their caregiver gives consent, an AOD screening tool and brief assessment information.

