
### Outcome Measures: Follow-Up Interviews

The timeline followback (TLFB) method [83] is the gold standard method for collecting youth report retrospective estimates of AOD use using a calendar visual aid to facilitate recall. This study used a computer-administered and calendar-assisted instrument created for REDCap-compatible remote asynchronous follow-up assessment modeled after the TLFB [31]. This version assesses the number of days that youth used alcohol, tobacco, marijuana, non–medical prescription drugs, inhalants or vapes, and herbs or synthetic drugs over the past 90 days. If alcohol was used, follow-up questions assess binge drinking episodes. The KIDSCREEN-27 questionnaire (youth and caregiver report) [84] measures youth functioning in social and school domains. Items assess the degree to which youth have experienced problems with a specific task or activity during the past month. It is internationally used and has excellent psychometric properties with strong construct validity and test-retest reliability [84,85]. The Services Assessment for Children and Adolescents (caregiver report) [86] assesses the youth’s past and current use of inpatient, outpatient, and school-based behavioral health services. It has shown strong validity and test-retest reliability [87] as well as interrater reliability between parent and child reports [88]. Items were added to assess caregiver enrollment and the use of web-based educational and support resources for adolescent AOD. Perceived Risk (youth report) [89] asks youth to rate the degree to which people risk harming themselves if they use various categories of substances on a 4-point scale ranging from *no risk* to *great risk*. Peer Deviance (youth report) [89] assesses the number of peers who use various substances on a 5-point scale ranging from *none* to *all*. Parent Rules about Substance Use (youth and caregiver report) [90] assesses parent rules about using various substances on a 6-point scale ranging from *not allowed to use AOD* to *no rules about using AOD*. The Family Assessment Device (youth and caregiver report) [91] assesses family relationships, communication, and problem-solving on a 4-point scale ranging from *strongly agree* to *strongly disagree*. The Comprehensive Adolescent Severity Inventory (youth report) [92] assesses academic achievement, school connection, and disciplinary record. Youth-Provider Connectedness (youth report) [93] assesses the level of trust and connection adolescents feel toward their health care providers on a 5-point scale ranging from *not at all* to *very much*. Psychoeducation Knowledge (caregiver report; created for this study) assesses caregiver knowledge of the tablet-delivered AOD psychoeducation. The Parent-Adolescent AOD Communication Frequency measure, Parent-Adolescent AOD Communication Quality measure, and Brief Problem Monitor (all described in the previous subsection) are also administered at follow-up to youth and caregivers.

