
### Plan of Analyses

#### Aim 1 Analyses

Aim 1 evaluates the effectiveness of SBIRT-A-Family compared to SBIRT-A-Standard in preventing the escalation of AOD use. AOD use is measured using the TLFB, which computes the percentage of the days of use over the past 90 days across a range of substances. Given that we expect the percentage of the days of AOD use to be highly skewed within this population identified as predominantly low risk, we will collapse outcomes on this measure onto a 4-point ordinal scale indicating the levels of AOD use as follows: *none* (0% days of use), *once per month*
*or less* (1%-3% days of use), *between once per month and once per week* (4%-14% days of use), and *once per week or more* (≥15% days of use). Aim 1 hypotheses are tested using a mixed effects logistic regression model for ordinal longitudinal outcomes [94]:

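### The initial 90-day AOD calendar is completed after randomization and looks back from its own completion date, so post-visit days enter the value that the Aim 1 slope model takes as its start

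*Protocol article*

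**What the plan says.** All references are to the Protocol article.

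- **Timing of randomization and intervention** (Recruitment, Randomization, Intervention Flow, and Outcome Assessment Procedures): the section opens with the statement "Study recruitment and randomization as well as all SBIRT-A activities occur on the day of the visit in PC offices".
- **Timing of outcome assessments** (same section): data are collected remotely at "initial assessment (as soon as possible after the PC visit) and at 3, 6, 9, and 12 months after the PC visit". The later waves are dated from the visit. The first is dated only as soon as possible after it.
- **Look-back** (Outcome Measures: Follow-Up Interviews): the calendar-assisted instrument counts days of use of each substance, the list ending with "herbs or synthetic drugs over the past 90 days". Aim 1 Analyses says the measure "computes the percentage of the days of use over the past 90 days across a range of substances".
- **Role of the first value** (Aim 1 Analyses): the slope parameters "estimate the linear rate of change (ie, slope) in the log odds of" the outcome, and a positive slope means "an increase in the log odds of being in a lower AOD use category on each logit over time compared to the initial assessment". The intent-to-treat effect is the difference between the two arms' slopes.
- **A use measure taken before randomization** (SBIRT-A-Standard Procedures, Screening): the CRAFFT "assesses the number of days during the past year and then the past 3 months during which various formulations of AOD were used". Both arms complete it, and the tablet randomizes the family after screening. Aim 1 does not name it as the baseline.

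**The concern.** The first calendar is treated as the untreated starting point, but it is taken after treatment has begun and its window slides with the completion date. If completed k days after the visit, it covers about 90 − k days before the visit and k days after it. Any early effect in those k days is absorbed into the start of the slope instead of counting as change.

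Other sections treat this wave in two incompatible ways. Fidelity Measures has families report at it which components they received, and Study Power counts it among the five follow-up measurements. Yet Study Power projects one common figure, 62.3%, for at-risk youth at that wave before the arms diverge. Evaluating Clinical Significance takes every normative-comparison youth to be in the lowest category at that wave by definition. A negative screen on the visit day cannot guarantee that for days after the visit.

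At stake is the Aim 1 estimate and any analysis that adjusts for the initial value, because that value is not a pre-randomization quantity.

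**Working it through.** **Inputs from the article.** 90-day look-back; waves coded TIME = 0 to 4; effect = slope difference; 1600 youth analysed (taken as 800 per arm); 62.3% in the lowest alcohol category at the start, 78.4% (Family) and 67.9% (Standard) at 12 months; within-person correlation 0.90; stated power 0.99. **Assumed:** the lag k, the same for all youth, and the time course of the effect.

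**Step 1: the plan's own figure.** The 12-month log odds ratio is ln(0.784/0.216) − ln(0.679/0.321) = 0.540 (odds ratio 1.72). A two-proportion calculation with 800 per arm gives power 0.997. A simulation of the slope contrast (lowest category versus any use, logistic model with robust standard errors, two-sided 5%) gives 1.00. The stated 0.99 is reproduced.

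**Step 2: loss in the slope.** With TIME = 0 to 4, the least-squares slope weights are (−2, −1, 0, 1, 2)/10. Let D be the effect and a = k/90 the post-visit share of the first window.

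- *Full effect from the visit, lasting.* Arm differences (a, 1, 1, 1, 1)·D give a slope difference of (2 − 2a)D/10. The fraction lost is a = k/90.
- *Effect growing linearly with time.* Window means are proportional to (k²/180, 45, 135, 225, 315), so the slope difference is proportional to (810 − k²/90)/10. The fraction lost is k²/72900.
- *Early effect that fades.* Arm differences (a, 1, ½, 0, 0)·D give −(1 + 2a)D/10. With D = 0.540 this is −0.054 at k = 0, −0.071 at 14 days and −0.090 at 30.

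| Lag k (days) | Loss, lasting effect (k/90) | Simulated slope difference | Simulated power | Loss, gradual effect (k²/72900) |
|---|---|---|---|---|
| 0 | 0% | 0.120 | 1.00 | 0% |
| 7 | 8% | 0.109 | 1.00 | 0.1% |
| 14 | 16% | 0.100 | 1.00 | 0.3% |
| 30 | 33% | 0.078 | 0.97 | 1.2% |
| 45 | 50% | 0.058 | 0.82 | 2.8% |
| 60 | 67% | 0.038 | 0.47 | 4.9% |

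The two simulated columns refer to the lasting effect, with 400 runs per row. In the gradual case simulated power stayed at 1.00 throughout. In the fading case the simulated slope difference was −0.050, −0.067 and −0.087 at 0, 14 and 30 days. It is negative even with a clean start, and delay moves it further from zero.

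**Step 3: analyses that do not use the initial value.** The raw 12-month log odds ratio stayed at about 0.53 to 0.55 at every lag in the lasting and gradual cases, with power 0.99 to 1.00.

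**Step 4: use as a covariate.** If the initial value were a covariate with coefficient b, the adjusted 12-month difference for a lasting effect would lose b·a. With b = 0.7 (an assumption), that is 0.7 × 16% = 11% at 14 days and 0.7 × 33% = 23% at 30.

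**Step 5: scale.** The simulation places k/90 of the effect directly on the log-odds scale, so it does not test whether that share carries over to the planned ordinal outcome. As an illustration, assume random (Poisson) use averaging m days per 90 and complete cessation at the visit. The share of the change in the probability of the lowest category that enters the start is [exp(−m(90 − k)/90) − exp(−m)] / [1 − exp(−m)]. For m = 1 this is 10% at 14 days and 23% at 30. For m = 3 it is 3% and 9%. Both are below k/90. Other category thresholds may behave differently.

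**The case against.** The strongest reply is that the practical loss may be close to nothing. The plan models change as a linear slope and projects both arms from one starting figure to different one-year figures. Under such gradual divergence the loss is about 1% even at 30 days. Study Conditions also lets providers complete interventions at a visit within 1 week, so for some families the first post-visit days precede the provider-facing content. At lags of 7 to 14 days power stays near 1.00 even in the worst case. All of this stands, and it limits the size of the point. It does not make the starting value a pre-randomization measure.

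A reader might infer more than the documents support:

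- *That the effect shrinks whatever model is used.* It does not. A 12-month contrast without the initial value, the Aim 3 logistic model, and an analysis using the visit-day CRAFFT as baseline all escape. A fading effect is distorted in another direction.
- *That counting the same days again at 3 months is itself a bias.* It is not. The 3-month window is meant to be post-visit; the distortion comes only from the starting value.
- *That the lack of a closing date is an error.* The schedule figure is not shown, and a completion window may be set in the full protocol. Such a window would cap k without removing post-visit days from the start.
- *That the lag is longest for the hardest-to-reach youth.* The article says "research staff members blinded to condition assignment reach out to arrange a live assessment", but that sentence concerns a missed follow-up assessment. Applying it to the initial wave is a reading, and no lag data are given.

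**Conclusion.** The point holds for any analysis that uses the initial calendar as slope origin or baseline covariate, which includes the planned Aim 1 model. Followed as written, the plan places k post-randomization days in a 90-day starting window.

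The size depends on two things the article does not give: the lag and the time course of the effect. The k/90 figures are the upper case considered, an immediate and lasting effect on the percent-days scale. They should not be read as the expected loss on the ordinal log-odds scale. At one to two weeks the main harm is an estimate understated by up to about 8% to 16%, not lost power. Power becomes a concern only if long lags (45 days or more in the simulation) coincide with an immediate, lasting effect.

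**What to change.** 1. Anchor the initial calendar to the 90 days ending the day before the primary care visit, a date the study already holds, and compute TIME from actual assessment dates.
2. For youth already assessed (recruitment began in March 2024), re-derive the window if the calendar stores dated entries. Dropping the k post-visit days leaves 90 − k pre-visit days, which then form the denominator.
3. If dated entries are not stored, report the lag by arm. Add a sensitivity analysis in all randomized at-risk youth that uses the CRAFFT past-3-month days, collected before randomization, as baseline in place of the initial calendar. The CRAFFT is a different instrument, so it fits more naturally as a covariate than as the first point of the same curve.
4. Do not restrict Aim 1 to youth assessed within a set number of days, such as 14. Response time is a post-randomization variable, and selecting on it gives up the protection of randomization.

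The cost is a date setting in the electronic form and a short amendment. Late responders must recall somewhat further back, and early enrollees will have a different window from later ones, which should be reported.
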